**Rule # 1: Comparing 1-year tumor regrowth rates between two arms.**

The analysis population of this monitoring rule is defined as patients who are included in the phase II portion final analysis AND achieve cCR status and choose WW strategy after completion of pre-operative TNT. The one-year regrowth rate will be defined as number of patients who experience tumor regrowth (regardless of whether it can be salvaged by TME) within one year after the last dose of pre-operative TNT divided by the total number of patients in the analysis population. The one-year regrowth rate will be estimated within each arm separately, when all patients in this population are followed for at least one year after last dose of chemotherapy. Based on Phase II design assumptions, the sample sizes

will be approximately 93 ( $=156 \times 0.593$ , critical value to reject phase II null hypothesis) and 78 ( $=156 \times 0.5$ , phase II control arm assumption) patients in Arm A and B, respectively.

DFS comparison between two arms will be noted to be concerning if the one-year regrowth rate in triplet TNT arm (Arm A) is much higher than that in the doublet TNT arm (Arm B). Thus, if:

- The difference in one-year regrowth rates (i.e., triplets arm minus doublets arm) is  $> 0.114$ , then the further accrual will be halted after discussion with CTEP.

This monitoring rule will provide 89% power to test the hypothesis that one-year regrowth rate in the triplet TNT arm (Arm A) is 42% versus that in the doublet TNT arm (Arm B) is 22%, i.e., 20% higher than that in doublet arm, at a one-sided alpha of 0.05.

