**Rule # 2: Comparing overall 1-year tumor regrowth rate (pooling two arms) to historical rate.**

The goal of this rule is to guard against an excessive regrowth rate that may be seen across the various NCTN sites. The International W & W Database [48] reported a 15.5% 1-year regrowth rate. However, the patients included in this retrospective database were not treated with TNT and cCR was determined by various and heterogeneous methods. It should be noted that these patients are taken from highly selected institutional case series, there is no denominator, non-uniform definitions of response, relatively short clinical follow-up, inconsistent surveillance protocols and variable patient selection criteria and neoadjuvant treatment regimens. The 1-year regrowth rate from this population is very likely a underestimation and may not be compatible with the setting of a modern clinical trial. Therefore, relying on prospectively collected data with uniform selection criteria and surveillance strategies similar to our trial, we can take into account the OPRA data. The OPRA data does have the limitation of therapy provided at primarily tertiary centers, but does provide the advantage of a prospective cohort of patients treated with TNT and subsequently followed in a manner identical to what we have described for the Janus Rectal Cancer Trial. Therefore, we consider a 1-year rate of local regrowth of 22% observed from OPRA trial as the “upper limit” of safety benchmark, i.e., it is considered not safe for patients if the 1-year rate of local regrowth in JANUS trial is larger than this benchmark.

The same population (i.e., assuming total of 171 NOM patients) and definition of 1-year tumor regrowth rate in Rule #1 will be applied to Rule #2. We consider a true 1-year regrowth rate of 32% or higher (alternative hypothesis) to be unacceptable and 22% or lower to be acceptable. If the observed 1-year regrowth rate is  $> 28.2\%$  (observed 6.2% increase), then the further accrual will be halted after discussion with CTEP. This monitoring rule will provide 85.6% power to detect if the true 1-year regrowth rate is unacceptable, i.e. 10% higher than historical rate of 22%, at a one-sided alpha of 0.025.

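### Regrowth Rule #1: the fixed limit of 0.114 has a one-sided type I error of about 0.036 at the 22% design rate, not the stated 0.05; the effect is small

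*Combined protocol and SAP*

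**What the plan says.** Section 13.5.1, Rule #1, compares one-year regrowth between arms among patients in the phase II final analysis who reach cCR and choose watch and wait. The expected numbers "will be approximately 93" on the triplet arm (156 x 0.593) and 78 on the doublet arm (156 x 0.5). The action limit is a fixed difference, triplet minus doublet: "> 0.114$ , then the further accrual will be halted after discussion with CTEP".

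The operating characteristics follow: "This monitoring rule will provide 89% power to test the hypothesis" that regrowth is 42% on the triplet arm, "versus that in the doublet TNT arm (Arm B) is 22%, i.e., 20% higher than that in doublet arm", "at a one-sided alpha of 0.05". The 22% is the OPRA one-year rate, given in the paragraph introducing the two rules with a 95% CI of 14-29%. Rule #1 names no other control rate and does not say which variance produced 0.114.

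Rule #2, on the pooled arms (171 patients), sets a limit of 28.2% against a 22% benchmark and claims "This monitoring rule will provide 85.6% power to detect if the true 1-year regrowth rate is unacceptable" at a one-sided alpha of 0.025.

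**The concern.** A type I error rate is a statement about the null, here equal regrowth in the two arms. With 22% in both arms, the 5% limit for a difference based on 93 and 78 patients is about 0.105, not 0.114. The stated limit equals 1.645 times the standard error at 42% versus 22%, that is, under the alternative. If so, the stated alpha and the stated limit do not belong together at the design rate.

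This is a rule for halting accrual over excess regrowth on the experimental arm, so those who act on it should have the right operating characteristics. The discrepancy runs towards fewer false alarms than declared, at the price of asking for a slightly larger observed excess before acting.

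**Working it through.** **Inputs** (all from Section 13.5.1): n_A = 93, n_B = 78; limit 0.114; alternative 42% versus 22%; null taken as 22% in both arms; one-sided alpha 0.05 (z = 1.645).

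**1. Reproduce the limit and the power.**
- SE under 42% versus 22%, unpooled: sqrt(0.42 x 0.58/93 + 0.22 x 0.78/78) = sqrt(0.002619 + 0.002200) = 0.0694.
- 1.645 x 0.0694 = 0.1142, which matches 0.114.
- Power, normal approximation: Phi((0.20 - 0.114)/0.0694) = Phi(1.239) = 0.892. Exact, summing the product of the two binomial distributions over all outcomes with a difference above 0.114: 0.890. The stated 89% is confirmed.

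Other constructions give different limits: null variance at 22%, 0.1046; null variance with continuity correction, 0.1164; pooled variance under the alternative, 0.1178 (unweighted) or 0.1186 (weighted). Only the unpooled alternative variance gives 0.114. This origin is inferred from the match. The error rate below does not depend on it.

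**2. Type I error at 22% in both arms.**
- SE under the null: sqrt(0.22 x 0.78 x (1/93 + 1/78)) = 0.0636.
- Normal approximation: 1 - Phi(0.114/0.0636) = 1 - Phi(1.792) = 0.0365.
- Exact double-binomial sum: 0.036.

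**3. Dependence on the common rate** (exact, 93 and 78 patients; 14-29% is the quoted OPRA interval; the test is the pooled difference-of-proportions test at one-sided p<0.05).

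| Common rate | Limit 0.114 | Limit 0.105 | Test, p<0.05 |
|---|---|---|---|
| 14% | 0.016 | 0.024 | 0.052 |
| 22% | 0.036 | 0.048 | 0.051 |
| 23% | 0.038 | 0.051 | 0.051 |
| 25% | 0.043 | 0.056 | 0.050 |
| 29% | 0.050 | 0.065 | 0.050 |

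Power at 42% versus 22%: 0.890 with 0.114, 0.915 with 0.105, 0.881 with the pooled test. The unpooled test has power 0.889 and exact size 0.053 at 22%.

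**4. Dependence on sample size.** The figures 93 and 78 count every cCR patient as choosing watch and wait. As an illustrative assumption, let about 80% do so, giving roughly 75 and 62. At a common 22%, exact alpha is then 0.053 with 0.114, 0.071 with 0.105, and 0.053 with the pooled test.

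**5. Size in patients.** One Arm A patient is 1/93 = 0.0108, more than the gap 0.114 - 0.105 = 0.009. With 17/78 regrowths on the doublet arm, both limits are first passed at 31/93 (0.3333 - 0.2179 = 0.1154; 30/93 gives only 0.1046). With 16/78, the limit 0.105 is passed at 29/93 (difference 0.1067) and 0.114 at 30/93 (0.1174).

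**6. Rule #2 for comparison.** 0.22 + 1.96 x sqrt(0.22 x 0.78/171) = 0.2821, matching 28.2%. The variance at 32% would give 0.2899. Its exact alpha is 0.0248, in line with the stated 0.025.

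**The case against.** **No null rate is stated.** Over the whole 14-29% interval, alpha at 0.114 never exceeds 0.05, so 0.05 could be read as an upper bound. This stands in part: 0.036 is a figure at one rate, not a property of the rule. But the plan does not call 0.05 a bound, 22% is the only control rate in the rule, and the bound fails if fewer patients choose watch and wait (0.053 in the illustration).

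**The choice of variance is defensible.** An unpooled variance is common in a two-sample comparison, and Rule #2 is a one-sample comparison with a fixed benchmark, where the null variance is natural. This stands. A reader might infer that the two rules contradict each other, or that the plan knowingly used the wrong variance. The documents support neither: they do not name a variance. What can be said is that Rule #2 meets its stated alpha at 22% and Rule #1 does not.

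**The consequence is trivial.** The stated power is right, the trigger moves by one patient at most, CTEP is consulted before any halt, Rule #2 guards the pooled rate, and the DSMB receives reports every six months. This stands, and it rules out reading the point as a material weakness in patient protection.

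**Conclusion.** The stated one-sided alpha of 0.05 is wrong for the fixed limit 0.114 at the design rate: the exact value is 0.036 with 93 and 78 patients and 22% regrowth in both arms. The stated 89% power is correct. The error is one of description and is minor, worth about 2 points of power (0.890 against 0.915 with a limit of 0.105) and no more than about one patient at the trigger.

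The 0.036 rests on the common 22% rate and on the planned numbers; it ranges from 0.016 to 0.050 over the OPRA interval.

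A reader might also infer that 0.105 is simply the correct limit. That does not follow. It comes close to 0.05 only near 22%, exceeds it above about 23%, reaches 0.065 at 29%, and gives 0.071 at 22% with about 75 and 62 patients.

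**What to change.** Either of two changes to Rule #1 is enough:

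1. State the rule as a one-sided p<0.05 difference-of-proportions test on the observed data, naming the pooled or unpooled form. This is the type of test that Section 13.4.2 already uses for cCR. It holds alpha near 0.05 whatever the common rate and the number choosing watch and wait. State power at 42% versus 22% as about 88% (pooled) or 89% (unpooled) for 93 and 78 patients.
2. Keep 0.114 and state alpha as about 0.036 at a common 22% rate, with the range 0.016 to 0.050 over 14-29%.

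In both cases, state the null rate and the variance used, and note that 93 and 78 assume every cCR patient chooses watch and wait. The cost is a sentence or two in Section 13.5.1. Option 2 leaves the rule itself unchanged, and neither option alters sample size or data collection.

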**Rule # 2: Comparing overall 1-year tumor regrowth rate (pooling two arms) to historical rate.**

The goal of this rule is to guard against an excessive regrowth rate that may be seen across the various NCTN sites. The International W & W Database [48] reported a 15.5% 1-year regrowth rate. However, the patients included in this retrospective database were not treated with TNT and cCR was determined by various and heterogeneous methods. It should be noted that these patients are taken from highly selected institutional case series, there is no denominator, non-uniform definitions of response, relatively short clinical follow-up, inconsistent surveillance protocols and variable patient selection criteria and neoadjuvant treatment regimens. The 1-year regrowth rate from this population is very likely a underestimation and may not be compatible with the setting of a modern clinical trial. Therefore, relying on prospectively collected data with uniform selection criteria and surveillance strategies similar to our trial, we can take into account the OPRA data. The OPRA data does have the limitation of therapy provided at primarily tertiary centers, but does provide the advantage of a prospective cohort of patients treated with TNT and subsequently followed in a manner identical to what we have described for the Janus Rectal Cancer Trial. Therefore, we consider a 1-year rate of local regrowth of 22% observed from OPRA trial as the “upper limit” of safety benchmark, i.e., it is considered not safe for patients if the 1-year rate of local regrowth in JANUS trial is larger than this benchmark.

The same population (i.e., assuming total of 171 NOM patients) and definition of 1-year tumor regrowth rate in Rule #1 will be applied to Rule #2. We consider a true 1-year regrowth rate of 32% or higher (alternative hypothesis) to be unacceptable and 22% or lower to be acceptable. If the observed 1-year regrowth rate is  $> 28.2\%$  (observed 6.2% increase), then the further accrual will be halted after discussion with CTEP. This monitoring rule will provide 85.6% power to detect if the true 1-year regrowth rate is unacceptable, i.e. 10% higher than historical rate of 22%, at a one-sided alpha of 0.025.

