## 13.2 Sample Size

We anticipate enrolling a maximum of 760 patients (380 per arm). We anticipate an accrual rate of 180 patients per year (15 per month) based on similarly accruing studies of Alliance N1048 trial, NRG-GI002, and the OPRA trial. The total accrual period of this study is estimated to be 4.2 years, including start-up time.

For phase II portion, per study design, total of 296 evaluable patients (148 per arm) will be needed to evaluate the primary endpoint. Up to an additional 16 patients (5% inflation) might be accrued to account for cancellation after randomization and major violations. Thus, the total targeted accrual for phase II portion will be up to 312 patients.

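### Both regrowth rules are sized on 156 accrued patients per arm, not the 148 evaluable per arm in their population, so Rule #2's fixed 28.2% limit delivers its stated one-sided 0.025 only near 171 watch-and-wait patients

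*Combined protocol and SAP*

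**What the plan says.** Section 13.5.1, Rule #1, defines the population as "patients who are included in the phase II portion final analysis AND achieve cCR status and choose WW strategy after completion of pre-operative TNT". It then sizes that population as 156 × 0.593 = 93 in Arm A and 156 × 0.5 = 78 in Arm B. The 0.593 is the smallest Arm A rate that would win phase II against a 50% control rate.

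Rule #2 takes over "The same population (i.e., assuming total of 171 NOM patients) and definition of 1-year tumor regrowth rate in Rule #1". Its hypotheses are: "We consider a true 1-year regrowth rate of 32% or higher (alternative hypothesis) to be unacceptable and 22% or lower to be acceptable". Its limit is an observed rate above 28.2% ("observed 6.2% increase), then the further accrual will be halted after discussion with CTEP"). Its operating characteristics are: "This monitoring rule will provide 85.6% power to detect if the true 1-year regrowth rate is unacceptable", that is, "10% higher than historical rate of 22%, at a one-sided alpha of 0.025".

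Section 13.2 says of phase II that a "total of 296 evaluable patients (148 per arm) will be needed to evaluate the primary endpoint". It allows up to 16 more patients (5%) for cancellations and major violations, hence a target of up to 312, or 156 per arm. Section 13.4.2 runs the phase II test on the mITT population. Section 13.4.1 limits that population to randomized patients who completed chemoradiation and started protocol chemotherapy. Section 7.3 lets a patient with cCR have either WW or surgery (TME).

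**The concern.** The definition and the sizing do not describe the same patients. The sizing starts from everyone accrued, including the 5% added because they are expected to drop out of the analysis. It multiplies by the cCR rate only. No factor represents the third condition, choosing WW, so uptake is implicitly 100%.

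This would matter little if the limit were set at the number actually observed. Rule #2 instead fixes a percentage, so its false-trigger probability depends on how many WW patients there are. The plan gives one error rate and one power, both for 171, and no way to reset the limit. Crossing it can lead to a halt in accrual while the 760-patient phase III is under way, so those overseeing the trial should know the rule's real error rate at the number the plan itself implies.

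**Working it through.** **Inputs.** Null rate 0.22, alternative 0.32, limit 0.282, stated number 171, stated one-sided alpha 0.025 and power 85.6% (Rule #2). Evaluable 148 per arm and accrual 156 per arm (Section 13.2). cCR rates 0.593 and 0.5 (Rule #1). WW uptake is not given, so any value below 100% is an assumption.

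**Formulas (normal approximation).**
- alpha = P(Z > 0.062 / √(0.22 × 0.78 / n))
- power = P(Z > (0.282 − 0.32) / √(0.32 × 0.68 / n))
- limit for alpha 0.025 = 0.22 + 1.96 × √(0.22 × 0.78 / n)

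**Reproducing the plan at n = 171.** √(0.1716/171) = 0.0317. The limit is 0.22 + 1.96 × 0.0317 = 28.2% and power is 85.6%. The plan's figures therefore come from this approximation at 171. With the limit rounded to 28.2%, alpha is 0.0252.

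**Number implied by the definition.** 148 × 0.593 = 87.8, about 88; 148 × 0.5 = 74; total 162 if every cCR patient chooses WW.

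**The fixed 28.2% limit at other numbers.** The exact columns use the smallest count above 28.2% of n.

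| n | Basis | Alpha, normal | Alpha, exact | Power at 32%, normal | Power, exact |
|---|---|---|---|---|---|
| 171 | plan | 0.0252 | 0.0248 (≥49) | 0.857 | 0.846 |
| 170 | one fewer | 0.0255 | 0.0334 (≥48) | 0.856 | 0.872 |
| 162 | 148 per arm, full uptake | 0.0284 | 0.0335 (≥46) | 0.850 | 0.858 |
| 146 | assumed 90% uptake (0.9 × 162 = 145.8) | 0.0353 | 0.0333 (≥42) | 0.838 | 0.822 |
| 145 | same, rounded down | 0.0358 | 0.0453 (≥41) | 0.837 | 0.854 |
| 130 | assumed 80% uptake (0.8 × 162 = 129.6) | 0.0440 | 0.0503 (≥37) | 0.824 | 0.831 |
| 173 | 148 per arm, 67% and 50%, full uptake (99 + 74) | 0.0245 | 0.0303 (≥49) | 0.858 | 0.869 |
| 214 | OPRA's WW entry, 120/166 × 296 | 0.0143 | 0.0153 (≥61) | 0.883 | 0.880 |

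The exact column is a sawtooth. It jumps from 0.0248 to 0.0334 when one patient is lost from 171, and from 0.0333 to 0.0453 between 146 and 145. The normal column isolates the effect of sample size.

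**Limit that restores 0.025 at n = 162.** Normal: 0.22 + 1.96 × 0.03255 = 28.4%, power 83.8%. Exact: 47 or more of 162 (29.0%), alpha 0.022, power 0.815.

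**Rule #1 (limit 0.114, 22% versus 42%), normal approximation.** At 93 and 78, the null standard error is √(0.1716 × (1/93 + 1/78)) = 0.0636, so alpha is 0.037. The alternative standard error is √(0.2436/93 + 0.1716/78) = 0.0694, so power is 0.892, matching the stated 89%. At 88 and 74, alpha is 0.041 and power 0.886. At an assumed 80% uptake (70 and 59), alpha would be about 0.060.

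**The case against.** The strongest reply is that the sizes are labelled as approximate or assumed, that 148 is a requirement rather than a ceiling, and that the effect is small. Much of this stands. The final analysis takes all treated mITT patients once target accrual is reached, so the base could lie between 148 and 156 per arm if losses are below 5%. At the design alternative of 67% in Arm A, 148 per arm gives 173, where the normal-approximation alpha is 0.0245. What does not stand is the stated pairing of 171 with a population that, on the plan's own evaluable number and the same 59.3% and 50% rates, comes to 162.

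Four stronger readings are tempting, and the documents do not support them.

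- A reader might infer that the false-trigger rate is about a third above the stated value (0.0335 against 0.025). That is the exact figure at 162, but 170 already gives 0.0334, so most of the excess is discreteness. On the approximation the plan used, the move is from 0.0252 to 0.0284.
- A reader might infer that the error keeps rising as the trial unfolds. It would rise if WW uptake is incomplete, but the documents give no uptake rate. OPRA's WW entry figure in Section 13.5.1, applied to 296, points the other way: about 214 patients and alpha about 0.015. The direction is undetermined.
- A reader might infer that excess regrowth could be missed or that accrual stops automatically. Power at 162 is essentially unchanged, and the halt follows discussion with CTEP.
- A reader might infer that Rule #1 fails too. At full uptake its 0.05 still holds and its power barely moves.

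**Conclusion.** The sizing base is inconsistent with the rules' own population definition and should be corrected. At the plan's evaluable number, with its 59.3% and 50% cCR rates and full WW uptake, Rule #2 has one-sided alpha of about 0.028 rather than 0.025, and power of about 85%. That is a small discrepancy. The more general weakness is that a fixed percentage carries a single quoted error rate although the number of WW patients is uncertain. By the normal approximation, alpha runs from about 0.044 at 130 patients to about 0.014 at 214; both ends rest on assumptions about WW uptake or entry that the plan does not make. Below 171 the consequence is more frequent triggering of the discussion that can halt accrual. The point does not bear on the cCR or DFS tests.

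**What to change.** In Section 13.5.1, replace 156 by 148 and the sizes by 88, 74 and 162, state the WW uptake assumed, and restate alpha and power for both rules. For Rule #2, choose one of the following:

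- Keep 28.2% and report alpha about 0.028 and power about 85% at 162, with a range over plausible numbers of WW patients.
- Define the limit at the realized number n, as 0.22 + 1.96 × √(0.22 × 0.78 / n), which is 28.4% at 162 with power about 84%. Alternatively use the exact count, 47 or more of 162, with alpha 0.022 and power 0.815.

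The change is to wording only and adds no patients. The first option costs nothing beyond disclosing a slightly higher error rate. The second holds the error rate (approximately by the formula, strictly by the exact count) but gives up some sensitivity to excess regrowth at 162: about one percentage point on the normal scale (85.0% to 83.8%), or about four with the exact count (85.8% to 81.5%). Because this is a safety rule, that trade should be made deliberately and recorded.

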**Patient safety monitoring:**

The safety monitoring rule specified below is based on OPRA data and the knowledge available at study development. We note that the patient safety monitoring rule may be adjusted in the event of either 1) the study re-opening to accrual (if paused) or 2) at any time during the conduct of the trial and in consideration of newly acquired information regarding the adverse event profile of the treatment(s) under investigation.

- If at any time in either arm we observe at least one of the following scenarios, then discussions among the Study Team, Alliance DSMB, and CTEP are required to assess whether modifications to the study are needed:

- During TNT treatment, in each arm separately, if 6 or more patients in the first 30 treated patients (or > 20% of all patients after 30 are accrued) experience a grade 4 or higher non-hematologic adverse event deemed at least possibly related to study treatment (i.e. an adverse event with attribute specified as “possible,” “probable,” or “definite”).

The Study Chair(s) and the Study Statistician will review the study monthly to identify accrual, adverse event/safety trends, and any emerging concerns.

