## 9.3 Expedited Adverse Event Reporting (CTEP-AERS)

Investigators are required by Federal Regulations to report serious adverse events as defined in the table below. The descriptions and grading scales found in the NCI Common Terminology Criteria for Adverse Events (CTCAE) version 5 will be utilized for AE reporting. The CTCAE is identified and located on the CTEP website at: [ctep.cancer.gov/protocolDevelopment/electronic\\_applications/ctc.htm](http://ctep.cancer.gov/protocolDevelopment/electronic_applications/ctc.htm). All appropriate treatment areas should have access to a copy of the CTCAE. All reactions determined to be "reportable" in an expedited manner must be reported using the Cancer Therapy Evaluation Program Adverse Event Reporting System (CTEP-AERS).

For further information on the NCI requirements for SAE reporting, please refer to the 'NCI Guidelines for Investigators: Adverse Event Reporting Requirements' document published by the NCI.

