#### Death

Death due to progressive disease should be reported as Grade 5 “Disease progression” in the system organ class (SOC) “General disorders and administration site conditions.” Evidence that the death was a manifestation of underlying disease (e.g., radiological changes suggesting tumor growth or progression: clinical deterioration associated with a disease process) should be submitted.

Any death occurring within 30 days of the last dose, regardless of attribution to the investigational agent/intervention requires expedited reporting within 24 hours.

Any death occurring greater than 30 days after the last dose of the investigational agent/intervention requires expedited reporting within 24 hours only if it is possibly, probably, or definitely related to the investigational agent/intervention.

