## 13.3 Power Justification

The design of this trial is a randomized, seamless phase II/III trial. After a patient is registered, they will be assigned to one of the two treatment arms in a 1:1 ratio utilizing a dynamic allocation algorithm based on the methods by Pocock and Simon [46].

The patients included in the phase II endpoints analyses will be included in the phase III endpoints analyses. The accrual will not be halted while waiting for phase II endpoints to be matured and analyzed, unless we experience unexpected rapid accrual and/or unacceptably high treatment toxicity, or other unforeseen situations. If the criteria for continuation have been satisfied at conclusion of phase II portion, to protect the phase III comparison, the actual results of the phase II portion will not be released beyond the Alliance DSMB.

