### 13.4.2 Primary Endpoint:

#### Phase II Portion:

Hypothesis testing analyses will be performed on mITT population. Sensitivity analyses will be performed on PP population.

- **Interim Analysis Decision Rule:** An interim analysis will be performed when 50% (74 in each arm) of patients are randomized and cCR status available. Difference of proportions test [33], [34] will be conducted to compare cCR rate in the experimental arm to cCR rate in the control arm. The estimated one-sided p-value will be compared to the following stopping boundaries:

| Testing: | One-sided P-value | Difference in proportions | Decisions                                                                                                                                                                                                            |
|----------|-------------------|---------------------------|----------------------------------------------------------------------------------------------------------------------------------------------------------------------------------------------------------------------|
| Futility | > 0.44            | < 0.012                   | Reject H1: concluding that the chance of cCR rate of the experimental arm being superior to the control arm is too low to continue the study. The accrual will be terminated if it does not reach target enrollment. |

If futility boundary is not crossed, then the trial will continue accrual and patient follow-up per protocol. The trial will not be halted while performing the interim analysis. However, if the accrual is especially rapid, we may temporarily suspend accrual to avoid missing important acute toxicity patterns and assigning patients to potentially ineffective treatment (futility of cCR rate endpoint in experimental arm).

- **Final Analysis Decision Rule:** If the trial continues after the interim analysis, the final cCR rate analysis will be performed when target accrual is reached and the cCR status are available on all treated patients. Difference of proportions test will be conducted to compare cCR rate in the experimental arm to cCR rate in the control arm. If the one-sided p-value of the comparison is < 0.05 (difference in proportion > 9.3%), then we will conclude the cCR rate in the experimental arm is superior to the control arm.

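### The one adverse-event count rule gives a related death the same weight as a grade 4 event, so two or three related deaths in an arm's first 30 patients would usually not by themselves require the Study Team, DSMB and CTEP discussion

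*Combined protocol and SAP*

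**What the plan says.** The Patient safety monitoring part of Section 13.5.1 introduces a list of scenarios but gives only one. During TNT, in each arm separately, the rule counts patients who "experience a grade 4 or higher non-hematologic adverse event deemed at least possibly related to study treatment". The limit is 6 or more of the first 30 treated patients, then more than 20% of all patients once 30 have been accrued. If it is met, "then discussions among the Study Team, Alliance DSMB, and CTEP are required to assess whether modifications to the study are needed". The plan gives no tolerable event rate, error rate or power for this rule.

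Other provisions bear on deaths:

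- **Expedited reporting (Section 9.3.3, Death).** "Any death occurring within 30 days of the last dose, regardless of attribution to the investigational agent/intervention requires expedited reporting within 24 hours". A later death is reported on the same timescale if it is at least possibly related. Section 9.3 routes these reports through CTEP-AERS.
- **Monthly review (Section 13.5.1).** The Study Chair(s) and Study Statistician "will review the study monthly to identify accrual, adverse event/safety trends, and any emerging concerns".
- **DSMB reports (Section 13.5.2).** Every six months.
- **Power to adjust (Section 13.5.1).** The safety rule may be changed "at any time during the conduct of the trial and in consideration of newly acquired information regarding the adverse event profile".
- **Accrual clauses.** Section 13.3 says accrual will not be halted while phase II endpoints mature, "unless we experience unexpected rapid accrual and/or unacceptably high treatment toxicity, or other unforeseen situations". Section 13.4.2 says that if accrual is especially rapid, "we may temporarily suspend accrual to avoid missing important acute toxicity patterns". Neither gives a toxicity figure.
- **Early-off-treatment (EOT) rule (Section 13.5.1).** Death and toxicity are among the reasons counted. The arms are compared at 44, 87 and 131 patients per arm, with boundaries of 22.0%, 10.4% and 6.7% on the difference. Crossing one leads to data review and consultation with CTEP.

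**The concern.** The trial adds irinotecan to neoadjuvant treatment given with curative intent, and the protocol's own drug information foresees fatal toxicity. The irinotecan nursing guidelines (Section 10.6) warn that grade 4 diarrhea together with grade 4 neutropenia may lead to sepsis and potentially death.

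The sponsor has already decided that, at some count, three parties must confer. That count does not distinguish a treatment-related death from a grade 4 event the patient survives. It also leaves out hematologic events, so a related death classed as hematologic adds nothing to it. After two or three related deaths in one arm, nothing in this document would oblige the joint discussion to take place. The DSMB's next scheduled look could be up to six months away.

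**Working it through.** The plan states no operating figure for this rule, so there is none to reproduce beyond the limit itself: 6/30 = 20.0%, and the largest count that does not trigger is 5/30 = 16.7%.

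**Inputs.** From Section 13.5.1: limit of 6 in the first 30, per arm; EOT looks and boundaries. From Section 13.2: 760 patients. Assumed, because the documents give no figures: related mortality, and the rate q of related grade 4 non-hematologic events among the other patients. Patients are treated as independent.

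**1. Is the rule silent after k related deaths in the first 30?** With k related non-hematologic deaths, the rule stays silent if at most 5 − k of the remaining 30 − k patients have a qualifying grade 4 event:

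P(silent | k) = P(Bin(30 − k, q) ≤ 5 − k)

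For k = 2 and q = 0.05: P(Bin(28, 0.05) ≤ 3) = 0.238 + 0.350 + 0.249 + 0.114 = 0.951.

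For k = 3 and q = 0.05: P(Bin(27, 0.05) ≤ 2) = 0.250 + 0.356 + 0.243 = 0.849.

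| Related deaths k | q = 2% | q = 5% | q = 10% |
|---|---|---|---|
| 2 | 0.998 | 0.95 | 0.69 |
| 3 | 0.98 | 0.85 | 0.48 |

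The result depends on q. At 10% the rule stays silent after three deaths in just under half of cases.

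**2. How likely are such counts?** P(2 or more related deaths in 30) is 0.12 at 2% mortality and 0.45 at 5%.

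**3. Would the EOT rule catch them?** Excess deaths in one arm as a share of that arm, if nothing else differs between arms:

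| Patients per arm | 2 deaths | 3 deaths | Boundary |
|---|---|---|---|
| 44 | 4.5% | 6.8% | 22.0% |
| 87 | 2.3% | 3.4% | 10.4% |
| 131 | 1.5% | 2.3% | 6.7% |

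It would not. The rule also covers only patients who completed LCRT and started chemotherapy.

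**4. Cost of a single-death trigger.** Expected related deaths over the whole trial: 760 × 0.01 = 7.6 and 760 × 0.02 = 15.2.

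**The case against.** The strongest reply is that this is a design preference and not an error. Nothing in the rule contradicts another section. CTEP receives each qualifying death through its own reporting system, the chairs and statistician look monthly, the DSMB sees data every six months, and the rule can be changed at any time. A regimen that kills patients would probably also cause grade 4 events and early stops, which would push both numeric rules towards their limits. Nor can one see from here whether the DSMB's own procedures, or the standard Alliance monitoring procedures that Section 15.0 invokes, already call for ad hoc review of a related death.

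Most of this stands. It limits the point to what this document requires, and to a missing obligation to confer. It does not supply the trigger: none of these provisions sets a death count at which the three parties must meet.

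A reader might infer three stronger things that the documents do not support:

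- **That deaths would go unnoticed.** They would not, given 24-hour reporting and monthly review.
- **That five related deaths in 30 passing without a discussion is the realistic risk.** Five with no other qualifying patient is indeed below the limit. But five or more has probability 0.0003 at 2% mortality and 0.016 at 5%, and the rule would then stay silent only if none of the other 25 patients qualified: 0.28 at q = 5%.
- **That the rule is weak because it seldom fires over a full arm of 380.** At total qualifying rates below 20%, seldom firing is what a 20% limit is meant to do.

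**Conclusion.** The point holds as a cheap improvement to consider. In this document, the only adverse-event count rule does not separate related grade 5 from grade 4 non-hematologic events and leaves out hematologic deaths. At an assumed 5% grade 4 rate in the other patients, two related deaths in an arm's first 30 leave the rule silent with probability 0.95, and three with probability 0.85. Over assumed rates of 2% to 10% the ranges are 0.998 to 0.69 and 0.98 to 0.48.

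The pooling and the missing death trigger are read directly from Section 13.5. The probabilities rest on assumed rates and independent patients. The gap is in the mandate to confer, not in the visibility of deaths, and it does not touch the error rates or sample size of either phase.

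**What to change.** Add a second scenario to the Patient safety monitoring list in Section 13.5.1, for example:

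*During TNT, in either arm, any grade 5 adverse event (hematologic events included) deemed at least possibly related to study treatment.*

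The consequence is the discussion the section already names, with no automatic halt. This brings the DSMB into the discussion of each related death without waiting for its six-monthly report.

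The cost is one sentence and no new data collection, since these deaths are already reported within 24 hours. The downside is extra ad hoc discussions, about 8 over 760 patients at an assumed 1% related mortality and 15 at 2%. If the sponsor finds that too many, it could set a less sensitive numeric limit and state how often that limit would fire across both arms. As one example, 2 in the first 30 and then more than 5% per arm, checked after every patient to 380, would fire at least once in the two arms with probability 0.13 at 1% and 0.41 at 2%.
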